### 2.2. Online Platform

An internet-based and GDPR (General Data Protection Regulation)-compliant study platform will be created using the Joomla 3.9 content management system (Open Source Matters, Inc., New York, NY, USA) [27]. Randomization will be stratified according to professional status (nurse or resident physician), prior NIHSS knowledge (limited, moderate, or extended), and institution by virtue of specific links displayed on the front page. Clicking on the appropriate link will automatically randomize the participant into one of two groups (video or e-learning) through the use of Gegabyte’s Random Article module [28]. A specific and straightforward registration form (Membership Pro, Joomdonation [29]) will then be displayed. Participants will have to enter and confirm a valid e-mail address, choose a secure password, and validate a captcha field. After clicking on the “Register” button, a generic email containing a data policy statement will be sent to the email address entered by the participant. Simultaneously, the participant will be automatically logged in and a first questionnaire will be displayed.

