### 2.3. First Questionnaire

This questionnaire (Table 1) is designed to gather all relevant demographic information regarding the participant and to obtain data regarding their prior NIHSS training and knowledge. It will be administered using the Community Surveys 5.6 component (CoreJoomla) [30].

Regular expression (Regex) rules will be used to avoid invalid data entry. A 5-point Likert scale (very low/not at all to very high/very much) will be used to record appropriate data.

After completing this first questionnaire, participants will be redirected to a first 50-question quiz designed to assess their baseline knowledge. This quiz is identical to the one used in our previous studies [18,19]. After completing this quiz, participants will be shown the training material they have been allocated to.

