### 2.6. Outcomes

The primary outcome will be the difference between the score on the 50-question quiz answered before and after following the allocated learning material. Secondary outcomes will be the overall performance in the pre-course 50-question quiz according to profession and prior NIHSS experience, performance in the same quiz undertaken one month after completion of the learning material (knowledge retention), time to course and quiz completion, user satisfaction with the learning method, user perception of the duration of the course, and probability that the user would recommend the learning material they have been allocated to a colleague.

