### 2.7. Participants and Sample Size

Seventy-two participants are required to have 80% chance of detecting a difference of 2 points in the post-course 50-question quiz between groups at the 5% significance level. A total of 120 invitations should be sent, and a participation rate of 60% will therefore be required.

Disclaimers and data policy statements will be displayed on the front page and on the registration page (through a link that will open these statements in a modal).

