### 2.8. Data Curation and Statistical Analysis

Stata 16 (StataCorp LLC, College Station, TX, USA) will be used for data curation and statistical analysis. Data will be curated by one author [name] ([name]), who will assign neutral names randomly to the e-learning group and the video group. The curated DTA file will then be transferred to another author [name] ([name]) for data analysis.

A univariate linear regression will be used to analyze the primary outcome. Then, a multivariable linear regression model will be generated with profession, prior NIHSS knowledge, and work center as adjustment variables. The conditions of application will be checked, i.e., the residues distributions normality assessed graphically on a histogram and the homoscedasticity using the residual-versus-fitted plot function in Stata.

The analysis of the same quiz undertaken one month later (knowledge retention) will follow the same procedure as the primary outcome.

The assessment of the distribution of the other continuous variables, i.e., time for course completion and time for quiz completion, will be done graphically and using the Shapiro–Wilk test in case of doubt. Data will be described as means (95%CI) or median (Q1–Q3) depending on what is applied. Then, a Student’s unpaired t-test or the Mann–Whitney U test will be applied.

The cross-sectional assessment of the performance in the pre-course 50-question quiz will be described overall and according to profession and prior NIHSS experience.

A sensitivity analysis will be performed by excluding those who have previously followed either the e-learning module or the video from Patrick Lyden [20].

User satisfaction, user course duration perception, and probability of recommendation will be assessed using a 5-point Likert scale and analyzed graphically, then using the Fisher’s exact test.

The data file will be uploaded to the Mendeley Data repository.

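### Fisher's exact test ignores the order of the 5-point Likert outcomes and costs power if the arms differ by a shift along the scale

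*Protocol article*

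**What the plan says.** Section 2.8 (Data Curation and Statistical Analysis) states: "User satisfaction, user course duration perception, and probability of recommendation will be assessed using a 5-point Likert scale". It then says that these outcomes are to be "analyzed graphically, then using the Fisher’s exact test". It mentions no collapsing of levels, trend test, rank test or ordinal model.

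Section 2.6 (Outcomes) lists all three as secondary outcomes, the last being the "probability that the user would recommend the learning material they have been allocated to a colleague". Table 2 marks the corresponding post-course items as 5-point Likert items but gives no anchors. The only anchors in the article are in section 2.3 and describe the first questionnaire: "A 5-point Likert scale (very low/not at all to very high/very much) will be used to record appropriate data".

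A rank test does appear in section 2.8, for completion times: "Then, a Student’s unpaired t-test or the Mann–Whitney U test will be applied". The sample size in section 2.7 is set on the quiz score alone: "Seventy-two participants are required to have 80% chance of detecting a difference of 2 points in the post-course 50-question quiz between groups". The type I error rate given with it is 5%.

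**The concern.** A Likert response is ordered. Fisher's exact test on a table of two arms by five levels treats the levels as unordered labels, so a steady move towards higher satisfaction counts no more than a patternless difference of the same rarity. Yet a directional effect is what the trial has reason to expect for satisfaction: section 1.1 says that highly interactive modules have improved it before. An omnibus test spreads its power over every possible pattern of difference, and at this sample size little power can be spared. The test also returns only a p-value, with no measure of how far apart the arms are.

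What is at stake is the chance of detecting a real difference in how users receive the two methods, and the ability to report its size. The knowledge outcomes are not involved.

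**Working it through.** **Inputs from the document.** There are two arms (section 2.2), 72 participants in total, 80% power, a 2-point quiz difference and a 5% level (section 2.7), and five response levels (section 2.8).

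**Assumptions.** Allocation is 1:1, so 72/2 = 36 per arm (the ratio is not stated). Tests are two-sided (not stated). Baseline Likert distributions and effect sizes are assumed, since the article gives none.

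**1. The plan's own figure.** The article gives no power figure for the Likert outcomes. Its 72 is for the quiz score, with no standard deviation stated. With n per arm = 2(z₀.₉₇₅ + z₀.₈₀)²·SD²/d², d = 2 and an assumed SD of 3: 2 × (1.960 + 0.842)² × 9/4 = 35.3, rounded up to 36, so 72 in total. The SD implied by 72 is 3.03. The figure can thus be matched but not confirmed. It is used here only for the 36 per arm.

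**2. Does Fisher's test use the order?** With column totals c_j, arm-1 counts a_j, arm size n₁ and total N, the conditional probability of a table is ∏ C(c_j, a_j) / C(N, n₁). The p-value sums this over all tables no more probable than the observed one. A product does not depend on the order of its factors, so permuting the five levels leaves p unchanged. This needs no assumption.

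**3. Comparator.** The tie-corrected Wilcoxon-Mann-Whitney test uses midranks r_j, with W = Σ a_j r_j and

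V = n₁n₂/[N(N−1)] · Σ c_j (r_j − (N+1)/2)²

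z = |W − n₁(N+1)/2| / √V

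**4. Simulation.** The shift is proportional odds: the odds of responding at or below each level are divided by OR. For example, 3/7/25/45/20% at OR 3 becomes 1.0/2.6/11.6/41.9/42.9%. Fisher p-values came from full enumeration, with 1,500 trials per cell. Power in %, Fisher vs rank test, 36 per arm:

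| Assumed baseline, levels 1 to 5 (%) | OR 2 | OR 3 | OR 4 |
|---|---|---|---|
| 10/20/40/20/10 | 18 vs 35 | 50 vs 72 | 72 vs 89 |
| 3/7/25/45/20 | 22 vs 34 | 49 vs 68 | 72 vs 86 |
| 5/10/30/35/20 | 23 vs 37 | 54 vs 71 | 72 vs 90 |
| 20/20/20/20/20 | 19 vs 36 | 51 vs 74 | 72 vs 89 |
| 1/3/11/40/45 | 23 vs 33 | 51 vs 64 | 70 vs 81 |

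The loss runs from about 10 to 23 points. With 5,000 trials at OR 3, the first, second and fifth baselines gave 49 vs 72, 50 vs 69 and 50 vs 64.

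**5. Type I error (OR 1).** Fisher 4.5 to 5.9%, rank test 4.5 to 5.4%. The simulation standard error is √(0.05 × 0.95/1500) = 0.6 points, so both are compatible with 5%.

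**6. In terms of participants.** At OR 3, in the three baselines rechecked, Fisher's test needs about 50 to 55 per arm to match the rank test at 36: 50/36 = 1.39 and 55/36 = 1.53, or roughly 40 to 50% more. At an assumed 25 per arm, OR 3 gives 34 to 38% vs 48 to 57%.

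**7. Collapsing first.** Fisher's test on levels 4-5 vs 1-3 at OR 3 gives 51%, 40% and 13% in those three baselines, so dichotomising does not recover the loss.

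**8. A case that goes the other way.** If the arms differ mainly in spread, for example 2/8/60/20/10% against 15/20/30/20/15%, Fisher's test has 70% power and the rank test 15%.

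**The case against.** Several objections stand and limit the point.

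- **Validity.** Fisher's test holds its level, so this is a choice between two valid tests. The outcomes are secondary, and the objectives in section 1.2 do not mention satisfaction, duration or recommendation.
- **Anchors.** A reader might infer that all three items run from very low to very high. Section 2.3 says this of the first questionnaire, and Table 2 gives no anchors. The duration item could plausibly run from too short to too long, with the best answer in the middle. The arms could then differ in spread, and step 8 shows that the rank test can do much worse there.
- **Direction.** A reader might infer that a significant result could not show which method is preferred. The plan displays the distributions before testing, and for a shift between two arms the graph shows the direction. What is missing is an estimate of size. A Mann-Whitney p-value alone would not supply that either, so an effect measure has to be named.
- **Null results.** A reader might infer that the present test invites a null result to be read as equal satisfaction, and that a rank test would cure this. It would not: at OR 2 the rank test itself has only 33 to 37% power.
- **Consistency.** Using Mann-Whitney for completion times does not make section 2.8 contradict itself. There it is the alternative to a t-test for continuous data.
- **Assumed magnitude.** The proportional-odds shift is a setting that favours the rank test, and the distributions are invented. The direction of the loss was the same in all 15 shift scenarios, but its size is indicative only.

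What the objections do not remove is that the article names the test. This is a stated method, not detail left to an analysis plan, and it discards the order in outcomes where a shift is the natural alternative.

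**Conclusion.** The point holds as a minor efficiency improvement. For satisfaction and recommendation, Fisher's exact test is valid but gives up roughly 10 to 20 percentage points of power against a consistent shift, slightly more in the least favourable scenarios, and yields no effect estimate. This rests on 36 per arm with 1:1 allocation, two-sided 5% tests, assumed Likert distributions and proportional-odds shifts of 2 to 4.

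For perceived duration the document does not settle the matter, because its anchors are not given. The documents do not support a stronger conclusion that the test is wrong, that the loss applies to all three outcomes whatever their scales, or that the trial's main results are at risk. The primary and retention analyses are unaffected.

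**What to change.** In section 2.8:

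- For satisfaction and recommendation, replace Fisher's exact test with the tie-corrected Wilcoxon-Mann-Whitney test. Report the probability of superiority (ties counted as one half) with a 95% CI, and keep the planned graph. An unadjusted proportional-odds odds ratio is optional. Adjusting such a model for profession, knowledge level and institution is not needed here and could be unstable with 72 participants and sparse levels.
- For perceived duration, state the anchors. If they are monotone, use the same rank test. If they run from too short to too long, keep Fisher's test. Record the choice before the data are analysed.

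The cost is a sentence or two of text and one effect estimate per outcome, with no new data and no change to the sample size. The downside is lower sensitivity to differences in spread rather than location, which the graph would still show.

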### 2.9. Ethical Considerations

The study protocol was submitted to the regional ethics committees of both university hospitals (Req-2021-00543), which waived the need for ethical approval as this study falls outside of the scope of the Swiss Human Research Act from 2011.

The study is scheduled to begin during the first semester of 2022.

## 3. Discussion

### 3.1. Main Considerations

This prospective, multi-centric, web-based, triple-blind (participants, investigators, data analyst) randomized controlled study comparing video-based and e-learning should help determine if a highly interactive e-learning module improves NIHSS knowledge and skills more efficiently than the traditional didactic video amongst a mixed population of stroke unit, neurology and neurosurgery ward nurses, and physicians with different levels of experience and expertise.

Results of previous studies have shown that knowledge acquisition was higher in medical students than in paramedics [19]. This is probably due to a better understanding of the neurological system and of clinical testing, even though participants within both groups had no prior NIHSS knowledge. The current study is the first to test the impact of the e-learning module on a population with pre-existing NIHSS knowledge.

Further, we should also be able to determine the impact of these learning modalities on knowledge retention at one month. The decline in performance has been shown to be nonlinear; among participants displaying a significant decline in knowledge retention at 3 months, half of them present a significant decline already after 4 weeks [35]. This time interval has been recently used [36]. Electronic health (e-health) literacy was already high in some countries prior to the COVID-19 pandemic [37] and should have considerably increased in the wake of this crisis. Therefore, determining the most efficient asynchronous distance learning modality to help health care workers improve their NIHSS knowledge is both timely and relevant.

Given the importance the NIHSS score plays in the diagnosis, treatment decisions, and follow-up of stroke patients [1], it is essential to ensure that the NIHSS application skills are maintained at a high level. The study design should also help us gain knowledge of the current performance of neurology and neurosurgery nurses and physicians, prior to any teaching intervention, by virtue of the first (baseline) quiz. This could help determine the necessity of recurrent training in these highly specialized wards to maintain high performance in NIHSS application. There is little reason to believe that the potential decline in NIHSS application knowledge this study could reveal would be different in other settings or countries, and the results obtained should therefore be generalizable.

### 3.2. Strengths and Limitations

Both pathways of the study require approximately two to four hours to be completed, and participants will be asked to repeat the 50-question quiz after one month. There is currently a high level of fatigue amongst hospital staff related to the COVID-19 pandemic [38]. Even though the personnel and the different hierarchies express a high level of enthusiasm for this type of study, uncertainty remains regarding the number of participants who will engage in this study, and attrition might be high [39]. Furthermore, even though each participant will have their own login and password, we will not have any way to ascertain that the quizzes will be completed by one person and not a group of colleagues. However, we will emphasize the single-person performance aspect of this study in the instruction page, and believe that the risk of such bias is low. Although we will specify that no external resources are allowed, we will have no way to verify that these have not been used (e.g., detailed NIHSS form or internet page with explanations). The temptation to do so can be important, especially when study subjects desire to prove that their baseline NIHSS knowledge is high. This could bias the results with an over-assessment of baseline knowledge. The heterogeneity of English and French proficiency among nurses and physicians of both hospitals could have an impact on the results of the study. The e-learning is entirely in French, and Dr. P. Lyden’s [20] original video is in English. To minimize this effect, the entire video (be it the extracts in the e-learning or the full video) has been subtitled in French. Further, participants will also be asked about their language proficiency in the initial demographic questionnaire, and the distribution assessed among groups. Finally, using a 50-question quiz to determine NIHSS knowledge cannot be considered as entirely representative of the actual clinical application of this scale. The video vignettes have, however, been validated in prior studies and should therefore represent an acceptable surrogate outcome [18,19]. Moreover, reusing the same 50-question quiz could lead to an improvement from one time to another due to a “priming effect” of the first questionnaire. However, this effect should be smoothed out given the randomization as it should occur similarly in both groups.

## Figures and Tables

**Figure 1 healthcare-09-01460-f001:**
[figure not shown]
Study design.

**Figure 2 healthcare-09-01460-f002:**
[figure not shown]
Table of contents of the interactive e-learning module.

**Figure 3 healthcare-09-01460-f003:**
[figure not shown]
Embedded video and quiz interaction.

**Figure 4 healthcare-09-01460-f004:**
[figure not shown]
Feedback displayed after a wrong answer.

**Figure 5 healthcare-09-01460-f005:**
[figure not shown]
Interactive slide used to remind or teach visual fields.

**Figure 6 healthcare-09-01460-f006:**
[figure not shown]
Interactive slide used to remind or teach the concept of extinction.

**Table 1 healthcare-09-01460-t001:** First questionnaire.

Page	Field	Original Question	English Translation
1	Demographics	Age	Age ^a^
		Genre	Gender ^b^
		Années d’expérience clinique au total	Number of years of total clinical experience ^a^
		Années d’expérience clinique dans un service de neurologie et/ou de neurochirurgie	Number of years of clinical experience in a neurology and/or neurosurgery ward ^a^
		Maîtrise du Français	French proficiency ^c^
		Maîtrise de l’Anglais	English proficiency ^c^
		Dans quel service travaillez-vous principalement: Unité Cérébrovasculaire—surveillance continue Unité Cérébrovasculaire-étage Etage de neurologie Soins intermédiaires de neurologie Etage de neurochirurgie Soins intermédiaires de neurochirurgie Autre	In which ward do you most frequently work: ^b^ Stroke unit-surveillance unit Stroke unit-regular ward Neurology ward Neurology intermediate care unit Neurosurgical ward Neurosurgical intermediate care unit Other
2	Prior NIHSS knowledge	Avez-vous effectué une formation interne du service pour apprendre à faire une évaluation NIHSS?	Have you completed an in house NIHSS training? ^b^
		Avez-vous complété une formation certifiante officielle NIHSS?	Have you completed the official NIHSS certification course? ^b^
		Nombre d’années de pratique avec l’échelle NIHSS	Number of years of clinical experience with the NIHSS scale ^a^
		Fréquence d’application du NIHSS: Plusieurs fois par jour Environ 1 fois par jour Environ 1 fois par semaine Environ 1 fois par mois Très rarement ou jamais	NIHSS use frequency: ^b^ Many times per day Circa once a day Circa once a week Circa once per month Almost never or never
		Je me sens à l’aise par rapport à l’application du NIHSS	I feel comfortable using the NIHSS ^c^

^a^ Regex: regular expression validation. ^b^ MCQ: multiple-choice question (only one answer accepted). ^c^ 5-point Likert scale.

**Table 2 healthcare-09-01460-t002:** Post-course questionnaire.

Page	Field	Original Question	English Translation
1	Prior NIHSS learning method exposition	Aviez-vous déjà suivi cette méthode de formation au NIHSS?	Had you already been exposed to this NIHSS learning method in the past? ^a^
		Quand avez-vous suivi cette formation? Il y a moins d’un mois Il y a moins de 6 mois Il y a moins d’un an Il y a plus d’un an Je ne me souviens pas	When did you undergo this training? Less than a month ago Less than 6 months ago Less than one year ago More than one year ago I do not remember
	Current training-context	Dans quel cadre avez-vous suivi cette formation? Demandée par mon service Trouvée cette formation sur internet par hazard Information recue par email	In which context did you undergo this training? Required by my employers Found it online by chance Information received via email
	Current training-satisfaction	Comment évaluez-vous le niveau de difficulté global de cette formation?	How would you access the overall difficulty level of this training? ^b^
		Que pensez-vous de la durée de cette méthode de formation?	What do you think about the duration of this training? ^b^
		Quel est votre niveau de satisfaction concernant la méthode de formation?	What is your level of satisfaction regarding the learning method? ^b^
		Recommanderiez-vous cette méthode de formation à vos collègues?	Would you recommend this training method to your colleagues? ^b^
		Avez-vous des commentaires supplémentaires?	Do you have any additional comments?

^a^ MCQ: multiple choice question (only one answer accepted). ^b^ 5-point Likert scale.

## Data Availability

Not applicable.
